# Directional versus ring-mode deep brain stimulation for Parkinson’s disease: protocol of a multi-centre double-blind randomised crossover trial

**DOI:** 10.1186/s12883-023-03387-0

**Published:** 2023-10-18

**Keywords:** Parkinson’s disease, Deep brain stimulation, Directional deep brain stimulation, Steering subthalamic nucleus

## Abstract

**Background:**

The effectiveness of Deep Brain Stimulation (DBS) therapy for Parkinson’s disease can be limited by side-effects caused by electrical current spillover into structures adjacent to the target area. The objective of the STEEred versus RING-mode DBS for Parkinson’s disease (STEERING) study is to investigate if directional DBS for Parkinson’s disease results in a better clinical outcome when compared to ring-mode DBS.

**Methods:**

The STEERING study is a prospective multi-centre double-blind randomised crossover trial. Inclusion criteria are Parkinson’s disease, subthalamic nucleus DBS in a ‘classic’ ring-mode setting for a minimum of six months, and optimal ring-mode settings have been established. Participants are categorised into one of two subgroups according to their clinical response to the ring-mode settings as ‘responders’ (*i.e.*, patient with a satisfactory effect of ring-mode DBS) or ‘non-responder’ (*i.e.*, patient with a non-satisfactory effect of ring-mode DBS). A total of 64 responders and 38 non-responders will be included (total 102 patients). After an optimisation period in which an optimal directional setting is found, participants are randomised to first receive ring-mode DBS for 56 days (range 28–66) followed by directional DBS for 56 days (28–66) or vice-versa. The primary outcome is the difference between ring-mode DBS and directional DBS settings on the Movement Disorders Society Unified Parkinson’s Disease Rating Scale – Motor Evaluation (MDS-UPDRS-ME) in the off-medication state. Secondary outcome measures consist of MDS-UPDRS-ME in the on-medication state, MDS-UPDRS Activities of Daily Living, MDS-UPDRS Motor Complications–Dyskinesia, disease related quality of life measured with the Parkinson’s Disease Questionnaire 39, stimulation-induced side-effects, antiparkinsonian medication use, and DBS-parameters. Participants’ therapy preference is measured at the end of the study. Outcomes will be analysed for both responder and non-responder groups, as well as for both groups pooled together.

**Discussion:**

The STEERING trial will provide insights into whether or not directional DBS should be standardly used in all Parkinson’s disease DBS patients or if directional DBS should only be used in a case-based approach.

**Trial registration:**

This trial was registered on the Netherlands Trial Register, as trial NL6508 (NTR6696) on June 23, 2017.

## Background

Bilateral deep brain stimulation (DBS) of the subthalamic nucleus (STN) is an established treatment for Parkinson’s disease [1]. The effectiveness of DBS can be limited by adverse-effects such as dysarthria, tonic muscular contractions, and paraesthesia [2]. These adverse-effects can be caused by electrical current spillover into adjacent structures near the motor part of the STN [2, 3]. In theory, the ability to steer the current away from areas which are linked to adverse-effects could help to reduce adverse-effects [4, 5]. By directing the current to the area corresponding to the greatest clinical effect and by avoiding areas which potentially cause adverse-effects, it may also be possible to use greater current amplitudes, potentially improving the efficacy of DBS. Experimental data [3, 6] and studies investigating therapeutic window width [7, 8] indeed suggest that DBS with the availability of directional (*i.e.*, steering) capabilities could have a favourable effect on the performance of DBS. The increased possibilities of directional DBS are accompanied by an increase in programming complexity and likely causes patient follow-up to be more time consuming [9, 10]. Therefore, studies are needed that assess whether the potential clinical improvement of this newer and more complex technology justifies a broad application [9]. In the context of evaluating the potential clinical benefit of directional STN DBS over ring-mode DBS in Parkinson’s disease, we considered three questions especially relevant. Firstly, does directional STN DBS lead to a greater symptom reduction when compared to ring-mode STN DBS in patients who have an unsatisfactory effect of ring-mode setting? Secondly, does directional STN DBS lead to even further symptom reduction when compared to ring-mode STN DBS in patients who already have a satisfactory effect of ring-mode setting? Thirdly, does the entire STN DBS patient population (*i.e.,* the two aforementioned populations pooled together) experience a greater symptom reduction with directional STN DBS when compared with ring-mode STN DBS? This last question is also clinically relevant, as it may lead to standardly implementing directional instead of ring-mode STN DBS from the start of therapy. We initiated a clinical trial to answer these three questions.

## Methods

### Study design

We use a multi-centre double-blind randomised crossover trial to assess whether directional STN DBS is more efficacious than ring-mode STN DBS for the treatment of Parkinson’s disease motor symptoms (see Fig. 1). We defined directional DBS as the form of stimulation in which at least one of the two electrodes is programmed to emit electrical current in a specific direction, leading to a non-circular shape of current distribution in the horizontal plane. In effect, any other setting than the even distribution of current between the three contacts on one level (*i.e.*, each of the three contact emits one third of the total current) is considered directional. Ring-mode DBS is the form of stimulation in which the electrical current is emitted omnidirectionally in a horizontal plane. Participants have Boston Scientific® or Medtronic Sensight® directional electrodes implanted for DBS treatment. These electrodes have two contacts from which only omnidirectional current can be emitted (the most ventral and most dorsal contact) and six contacts distributed over two levels which are capable of emitting omnidirectional current (*i.e.*, three contacts are used simultaneously and equally) or emit current in a specific direction (all other configurations).

**Fig. 1 Fig1:**
[figure not shown]
Flowchart of the STEERING trial

### Participants

The inclusion criteria are (a) patients with bilaterally implanted Boston Scientific® or Medtronic Sensight® directional electrodes in the STN for the treatment of Parkinson’s disease; (b) at least six months follow-up after implantation of the DBS system; (c) optimal ring-mode DBS settings have been achieved as judged by the physician or nurse specialist and it is anticipated that further adjustment of ring-mode settings will unlikely lead to further motor improvement or would lead to stimulation-induced adverse-effects; and (d) age 18 years and older. Exclusion criteria are (a) legally incompetent; (b) active psychosis; (c) no written informed consent; and (d) no relevant motor symptom suppressing effect in ring-mode DBS on one of the steerable levels.

Patients were recruited from the DBS-clinics of Amsterdam University Medical Centers and the University Hospital of Cologne. Although not formally incorporated in the in- and exclusion criteria, participants had not been subjected to directional DBS before recruitment because this was not applied for Parkinson’s disease in Amsterdam UMC and not in the University Hospital of Cologne other than the previously published cases [11, 12].

### Study procedures and randomisation

If a patient meets the eligibility criteria, the treating neurologist or nurse specialist briefly introduces the study and provides the patient with written information about the study. If the patient is interested in participating, an appointment is made for an extra eligibility check and written informed consent. Each DBS patient is treated by a team consisting of a nurse specialist and a neurologist. Patients were classified as a ‘responder’ (*i.e.*, patient with a satisfactory effect of ring-mode DBS) or a ‘non-responder’ (i.e., patient with a non-satisfactory effect of ring-mode DBS) at the discretion of the treating physician or nurse specialist. The terms satisfactory and unsatisfactory were not further specified.

During the first study visit, the patient is seen in ‘off-medication’ state, defined as a withdrawal from dopaminergic medication for a minimum of 12 h. During the visit, DBS is turned off bilaterally (‘off-stimulation’). In the responder group, patients choose on which side they want the directional stimulation to be performed. Because parkinsonian symptoms are mostly asymmetrical, patients oftentimes have a preference for a specific side. For the non-responders, the researcher together with the patient identifies which electrode is associated with the most bothersome symptoms, based on remaining motor symptoms and/or stimulation-induced adverse-effects. Then, a directional monopolar review is performed on this electrode in which all eight individual contacts of the electrode are tested for rigidity control and adverse-effects thresholds. Depending on the findings and the participant’s preferences, a similar process can (but does not necessarily have to) be repeated for the other electrode at a later study visit prior to randomisation. As a result, the directional DBS setting of each participant can consist of one electrode with directional current configuration and one electrode with ring-mode configuration, or of two electrodes with directional current configuration. For the final directional setting before randomisation, at least one of the electrodes must be programmed in a directional current configuration. It is possible that an electrode which was used for monopolar directional review is still used in a ring-mode configuration in the final directional setting.

During the directional monopolar review, each of the eight contacts on the electrode are tested by slowly increasing the amplitude whilst measuring rigidity on the contralateral wrist. If rigidity cannot be adequately measured, other symptoms such as tremor or bradykinesia are used to determine the efficacy threshold. Once this threshold has been determined, the current is slowly increased further until an amplitude is reached which causes an intolerable stimulation-induced adverse-effect (this excludes symptoms such as transient paraesthesia, which tend to abate in the course of minutes without alteration of stimulation settings). The interval between the efficacy threshold and the adverse-effect threshold is considered the therapeutic window for the tested contact. Upon completion of this process for all eight contacts of the electrode, one to three new ‘directional programs’ are programmed into the device, based on therapeutic window width and efficacy threshold data from the directional monopolar review, complemented by clinical insight from testing multiple different stimulation configurations. In these new programs, margins for adjusting stimulation amplitude are set-up for later adjustments. Additionally, the ring-mode program that the patient had before enrolment in the study is kept as one of the programs on the device, which can be used as an ‘escape option’ by the patient if the newly programmed configurations have a worse clinical effect than the ring-mode program. Other DBS-parameters such as frequency and pulse width are not changed during the course of the trial.

After this initial visit, an optimisation period is implemented. In order to reflect the normal clinical practice in DBS programming for Parkinson’s disease, no formal duration or visit schedule is established for this period. Instead, visits and telephone consultations are planned as needed. Changes in stimulation parameters are recorded. The end of the optimisation period is reached when the researcher and the patient agree that the new – directional – stimulation program is as good or better than the ring-mode program, and further programming efforts are not likely to lead to a substantial improvement of Parkinson’s disease symptoms. When this program is considered to be stable (as a rule of thumb a period of at least two weeks without the need for adjustments is considered stable), the patient can be randomised.

At the randomization visit, the researcher records their prediction of whether or not the directional program will lead to a greater improvement of Parkinsonian symptoms when compared to the ring-mode. Patients are randomised into a crossover study design using ALEA randomisation software (www.aleaclinical.eu). Allocation is set to a 1:1 ratio with block sizes of two and four. Patients are stratified by their responder/non-responder status. Each participating patient receives both directional and ring-mode DBS treatment for a period of two months (56 days, with an accepted range of 28 to 66). Patients are randomised to receive directional stimulation as the first intervention and ring-mode stimulation as the second (directional-first group) or to receive the two interventions in reversed order (ring-mode-first group). The physician co-investigators and nurse specialists performing the programming are not blinded to patient allocation. Participants and trial nurses doing the assessments are blinded to the DBS settings (*i.e.*, ring-mode or directional DBS). The statistician analysing the results of the trial will be blinded as well.

At the end of the first intervention visit (*i.e.*, before cross-over) and at the end of the second intervention visit (*i.e.*, at the end of follow-up) the primary and secondary outcome measurements and questionnaires are performed. At the end of the second intervention, whilst still in blinded condition, the patient chooses which of the two programs they want to keep: the first or second intervention. After the participant finished all assessments, they may be unblinded and return to regular DBS follow-up.

Approval of the medical ethical committee of both participating centres was obtained. The STEERING-study conforms to the principles of the Declaration of Helsinki (version 2008). Study monitoring and data management are performed in accordance with the International Conference on Harmonisation—Good Clinical Practice guidelines. It is an investigator-initiated study. Funding organizations did not have an influence on the design, execution, data analysis, or participation in article drafting.

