## Discussion

Due to the broad distribution of recent advances in DBS technology, the implementation of directional DBS is feasible in standard care for Parkinson’s disease patients. This may lead to an increase in programming time and effort, possibly constituting an added burden for patients and clinicians alike [9]. For clinical practice, it would be of added value to know whether directional DBS leads to a clinical improvement in patients who already experience a good effect from ring-mode DBS, and in patients who experience a sub-optimal effect from ring-mode DBS. In order to investigate whether the use of directional STN DBS has a more beneficial effect on the motor symptoms of Parkinson’s disease when compared to ring-mode DBS, we use a randomised, double-blind crossover trial design. Some of the choices made in the study protocol warrant discussion.

First, we discuss performing three separate analyses for responders, non-responders and these two study populations pooled together. It is possible that there is a difference in added value of directional STN DBS when compared to ring-mode STN DBS for responders but not for non-responders, or vice-versa. Another possibility is that both responders and non-responders have added benefit from directional STN DBS, but to a different degree. Pooling responders and non-responders allows for a representative sample of the entire patient population of patients with Parkinson’s disease who received DBS treatment. If a significant difference is found between directional and ring-mode settings in the favour of directional STN DBS, this would mean we could implement directional STN DBS as the new treatment standard. Additionally, the pooled analysis will have greater power due to the higher number of subjects.

A second relevant issue is that it was not required for randomisation to have directional setting bilaterally. This approach was chosen because the most often cited reason to employ directionality is the occurrence of stimulation-induced adverse-effects [9]. These adverse-effects are not necessarily present at both sides within therapeutic current amplitudes. Another reason to opt for this approach is that a comprehensive directional monopolar review is a time-consuming effort, which can be burdensome for the patient. Hence, we anticipated that this approach warrants the best external validity.

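### The pooled result will apply to patients established on ring-mode in whom an acceptable directional program was found, not to all STN DBS patients and not to first programming

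*Protocol article*

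**What the plan says.** Two rules in Study procedures and randomisation govern entry to the randomised phase. First, optimisation ends when researcher and patient agree that the new directional "stimulation program is as good or better than the ring-mode program" and that further programming would add little. Once the program is stable, randomisation can follow: "a period of at least two weeks without the need for adjustments is considered stable), the patient can be randomised". Second, for the final directional setting, "at least one of the electrodes must be programmed in a directional current configuration". The article describes no other route to randomisation.

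Participants requires "at least six months follow-up after implantation of the DBS system" and ring-mode settings that are already optimised. It also excludes patients with no relevant ring-mode effect on a steerable level.

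The stated inferences are wider. The third question in Background begins "Thirdly, does the entire STN DBS patient population", and its relevance is explained by saying that "it may lead to standardly implementing directional instead of ring-mode STN DBS from the start of therapy". The Discussion states: "Pooling responders and non-responders allows for a representative sample of the entire patient population". Of a significant result in favour of directional stimulation it says "this would mean we could implement directional STN DBS as the new treatment standard".

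**The concern.** The agreement that opens the way to randomisation is a judgement on the same two treatments that the trial compares. It is made before any blinding begins, by a researcher who programmed the new settings and a patient who still has the old ring-mode program on the device as a fallback. Patients who do not reach agreement are never randomised, and an intention-to-treat analysis that starts at randomisation cannot bring them back.

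At stake is the trial's broadest claim. The Abstract says that the trial will inform a choice between directional DBS for everyone and directional DBS case by case. Randomising only patients in whom a directional program proved acceptable is already a form of case-by-case selection. A positive result in that set does not separate the two options.

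The start-of-therapy inference has a separate weakness. It arises from the eligibility criteria, because nobody is compared at first programming.

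**Working it through.** The plan gives no figure on this point: no expected pass rate, and no distribution of individual benefit. There is nothing to reproduce, so the check is a comparison of passages followed by an illustration with assumed inputs.

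**Comparison of passages**

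- Population asked about (Background, question 3): all STN DBS patients. Population randomised (Study procedures and randomisation): those with a stable directional program judged at least as good as ring-mode, directional on at least one electrode.
- Timing inferred (Background): start of therapy. Timing studied (Participants): six months or more after implantation, with ring-mode already optimised.
- Representativeness (Discussion): attributed to pooling the two strata. The 64 to 38 mix comes from two separate sample size calculations (Statistics), and the article does not link it to the mix of patients in practice.

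**Illustration**

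Assume that true individual benefit (in MDS-UPDRS-ME points, positive favouring directional) is normal with mean m and SD s. Let the judgement correlate r with true benefit, and let a share p of patients pass.

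- Mean among those randomised = m + r × s × φ(z)/p, where z is the normal quantile of p and φ is the standard normal density.
- Value of trying directional and otherwise keeping ring-mode = p × randomised mean, because those who fail count as 0.

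For p = 0.50, φ(z)/p = 0.399/0.50 = 0.798. For p = 0.90, φ(z)/p = 0.1755/0.90 = 0.195. For m = 2 and s = 4 with perfect selection at 0, p = Φ(0.5) = 0.691 and φ(z)/p = 0.352/0.691 = 0.509.

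| m | s | r | p | Randomised mean | Policy value |
|---|---|---|---|---|---|
| 0 | 4 | 1.0 | 0.50 | 4 × 0.798 = 3.19 | 1.60 |
| 0 | 4 | 0.5 | 0.50 | 0.5 × 4 × 0.798 = 1.60 | 0.80 |
| 0 | 4 | 1.0 | 0.90 | 4 × 0.195 = 0.78 | 0.70 |
| 0 | 4 | 0.5 | 0.90 | 0.5 × 4 × 0.195 = 0.39 | 0.35 |
| 2 | 4 | 1.0 | 0.69 | 2 + 4 × 0.509 = 4.04 | 2.79 |

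The rows with p = 0.90 represent a lenient criterion that few patients fail. With p = 0.50 and m = 0, varying s from 2 to 6 and r from 0.5 to 1 gives randomised means from 0.5 × 2 × 0.798 = 0.80 to 6 × 0.798 = 4.79. For scale, the plan's minimum important difference is 3 points in responders and 5 in non-responders.

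The shift can therefore be negligible or as large as the difference the trial is designed to detect, and the article does not allow a choice between these cases.

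**The case against.** The criterion has a sound rationale. Ring-mode must be optimised before entry, so randomising before the directional program is tuned would compare a finished setting with an unfinished one. The article also says that the optimisation period is meant to mirror ordinary practice. This stands, and it is why the randomisation rule should stay.

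Failures may be rare. Any uneven split of current on one level counts as directional, one electrode is enough, optimisation has no time limit, and ties satisfy the criterion. Patients without a useful effect on a steerable level are excluded beforehand, although that also narrows the population. The judgement is global, so its correlation with the off-medication motor score is unknown. All of this stands, and no size can be claimed.

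A policy of trying directional stimulation and otherwise keeping ring-mode dilutes the randomised effect but cannot reverse its sign. This stands too. A population mean of 0 describes directional stimulation for everyone, including patients already judged worse on it.

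Several of the practice statements are conditional in wording, and the Abstract keeps the case-by-case option open. That softens the claims, but the statement on representativeness carries no such condition.

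Finally, this is a condensed article and its flowchart is not visible, so the handling of patients who are not randomised cannot be called absent. The point does not need that. It sets one stated rule against stated conclusions.

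**Conclusion.** The concern holds as a limit on the target population. A positive pooled result would estimate the effect in patients established on optimised ring-mode in whom an acceptable directional program was found. It would not estimate the effect in all STN DBS patients, and the sample is not representative of them.

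Three stronger readings are tempting and are not supported:

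- **That the crossover comparison is biased.** Each randomised patient receives both settings in random order, so the contrast is valid for the randomised set. A null result would also be informative, because the set is if anything selected in favour of directional stimulation.
- **That the entry criterion rules out the start-of-therapy inference.** That limit comes mainly from the requirement of six months of follow-up and optimised ring-mode.
- **That the effect is inflated by about 3 points.** That figure needs a mean of 0, an SD of 4, perfect judgement and a 50% failure rate, none of which the article gives. Under the same assumptions the policy value is 1.6, and with 10% failures and a correlation of 0.5 the shift is about 0.4.

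The point should be fixed because question 3 carries the trial's widest practice claim. It does not undermine the primary comparison.

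**What to change.** Keep the randomisation rule and change the claim and one analysis.

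1. Restate question 3, and the Discussion's conclusion from the pooled analysis, as applying to patients established on optimised ring-mode in whom an acceptable directional program was found. Remove the representativeness statement and the start-of-therapy inference. The Discussion's later step from a benefit in responders to a directional review of all patients soon after surgery should be presented as a hypothesis.
2. For question 3, pre-specify a supplementary policy-level estimate beside the randomised-set estimate. Count consented patients who entered optimisation but never met the criterion as zero difference, on the assumption that they remain on ring-mode. State that these zeros are assumed, not measured, since the article describes outcome assessments only after randomisation. Report the number of such patients in each stratum.

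Consent precedes optimisation and stimulation changes are recorded, so these patients should be countable without new data collection. The cost is one extra analysis, a supplementary estimate closer to zero than the randomised-set estimate, and a narrower claim.
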